**Study drop out mitigation strategies: .**

If the watch is not worn for 7 consecutive days while reporting to work, study staff will ask the study participant about any discomfort related to study participation, and will encourage them to continue to wear the watch to the extent they are comfortable (indicating that we may miss data such as sleep).

We have extensive experience conducting randomized controlled studies and have successfully employed these methods in our prior research.

**BEHAVIORAL HEALTH RISK MANAGEMENT PLAN**

The enrollment for this study is not targeting persons with mental health conditions, and this study is not a clinical intervention study. Nevertheless, parts of the survey will ask respondents to recall unpleasant feelings and symptoms of depression. However, these questions are not diagnostic tools for depression or active intent to harm self/others. Responses to these questions are optional and participants may skip answering these questions if they choose.

Potential participants will be notified in the consent form that: "This study includes the assessment of depression symptoms; however, the study staff will not be actively monitoring for depression, treating depression, or referring you for treatment. If you experience depression, thoughts of suicide, or any other mental health concern during the study you will be responsible for arranging for medical care."

**D. Description, Risks and Justification of Procedures and Data Collection Tools:**

We do not foresee any adverse consequences for study participants. They will be asked to complete surveys in addition to wearing Smartwatches and sharing resulting physiologic data. The surveys and physiologic data from Smartwatches will be confidential and private. Database for this study will be password-protected and accessible only by authorized (by the study PI) research staff. All study datasets will be deidentified in accordance with HIPAA guidelines. Therefore, each study participant will be assigned a unique study subject ID number. Data collected from smartwatches and surveys will be linked to each subject ID number. For purposes of achieving the

analytic aims described above, inputs will include subject ID number, subject sex, data collected from smartwatches, and scores on surveys. Subject names, addresses, telephone numbers, or any other data that could serve as identifiers will not be entered into the study databases used for data analysis.

In regards to electronic data, we will use MS Excel for maintaining a list of participants, device serial number and basic information (e.g., department). The quarterly surveys will be collected via Mayo Clinic's Survey Research Center (they will send surveys to participants at both sites), which stores data from Qualtrics. Finally, smartwatch data will be collected via FitaBase - a 3rd party data aggregator which will not collect any PHI.

#### **E. Potential Scientific Problems:**

A potential problem is that participants wear the watches <50% of the time. This would render the data less usable for downstream analytics. Hence, we will monitor the smartwatch usage data on FitaBase, and if usage is <70%, we will request the participant to wear the watch as often or seek if there are any possible discomforts from the watches.

#### **F. Data Analysis Plan:**

For Aim 1, we will compare changes in outcome variables between Arm 1 (Smartwatch Intervention) and Arm 2 (Control group) at 6 months. Then, we will explore the durability of the benefits of having a Smartwatch for 12 months, by examining levels of well-being among Arm 1 participants at the 6- and 12-month mark. We will use generalized estimating equations to account for the repeated-measures design. Tests will be 2-sided, and we will use the intent-to-treat principle in analyses.

To determine whether continuous physiological measures (measured from Smartwatches) contain a 'signal' that predicts physician well-being, and if so in which dimensions. We will construct Probabilistic Graph Models (PGMs) for low overall well-being (score  $\geq 2$ ), burnout (score of  $\geq 27$  on emotional exhaustion scale or score of  $\geq 10$  on the depersonalization score), low quality of life ( $\geq \frac{1}{2}$  SD below the mean), high stress (score  $\geq 17$ ), and high fatigue (score  $\geq 11$ ). We will derive dynamics for these dimensions of well-being using dynamic Bayesian networks (DBN). Data from Arm 1 will be used to train MTL models to predict risk of low well-being, burnout, low QOL, high stress, and high fatigue in the next quarter. Models will be tested and retrained using data from subsequent assessments. We will then evaluate the predictions using data from Arm 2 (control). Standard metrics of model performance (e.g., AUC, sensitivity, specificity) will be reported. Predictor variables will be ranked by the relative importance in making predictions, and the top 10 predictors (a heuristic for simplicity in deriving easily interpretable predictions in English sentences) will comprise Core Well-being Factors. We aim to achieve predictive accuracies > 70%.

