**Study Aims:**

1. To determine if wearing a Smartwatch and having access to its physiological data (e.g., sleep, step count, activity, breathing reminders) improves well-being, and if so which well-being dimensions.
2. To determine whether continuous physiological measures (measured from Smartwatches) contain a 'signal' that predicts physician well-being, and if so in which dimensions.

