## **II. Background and Significance:**

Upwards of 40% of physicians have burnout. Physicians at the front lines of caring for patients with COVID-19 are at highest risk, and at least since 2011 burnout has been more prevalent among physicians than other US workers. Multiple systematic reviews and meta-analyses have concluded clinician burnout impacts quality of care in important ways. For example, studies of clinicians have found burnout is independently associated with medical error, medical malpractice suits, poor professionalism, absenteeism, low job performance, less favorable cost conscious attitudes, racial biases, lower competency, job dissatisfaction, patient dissatisfaction ratings across a variety of domains, and longer patient recovery times. Physicians with burnout are approximately twice as likely to quit their jobs and reduce clinical hours, resulting in a loss of productivity and access to care. At an organizational level burnout-attributable costs related to job turnover and reduced clinical hours among physicians alone are approximately \$7600 per physician each year with approximately \$4.6 billion in cost on a national scale. Additionally, studies have also found burnout to be independently associated with sleep impairments, alcohol abuse/dependence, suicidal ideation, and motor vehicle incidents. Physicians are at increased risk of suicide compared to the U.S. general population.

Unfortunately, burnout is underrecognized by those who suffer from it, and it typically goes undetected until physicians' performance or health deteriorates. There is a moral and business case to develop pragmatic ways to identify physicians at risk for burnout. In recognition of the broad impact of physician well-being on individuals, healthcare organizations, and society, The National Academy of Medicine's consensus study on clinician burnout (co-authored by PI [name]) "call(ed) upon leaders in health care organizations and health professions, educational institutions, as well as within the government and industry to prioritize, prevent and mitigate burnout and foster professional well-being for the overall health of individuals and the nation."

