Despite these recommendations from the National Academy of Medicine, few intervention studies have been conducted to-date involving residents and physicians to guide personal and organizational strategies. In previous randomized controlled studies, funded by the Physicians Foundation, we demonstrated that professional coaching reduced overall burnout and improved quality of life and resilience among physicians. It remains unknown, however, if physicians at risk for burnout or poor well-being in other dimensions will recognize it and proactively take steps to engage in professional coaching.

In this proposed study, we plan to conduct a 2-arm randomized controlled trial evaluating the effectiveness of 6 months of wearing a Smartwatch and having access to one's physiologic data to improve well-being among physicians. There is increased ubiquity of wearable technologies such as Smartwatches, that provide quantitative measures of one's physiological functioning (e.g., heartrate, sleep cycles, sleep quality) that may serve as a real-time surveillance mechanism to

forecast impending burnout or changes in other dimensions in well-being, potentially triggering individual intervention before suffering or negative impact to patient care occurs. We anticipate that providing physicians with individualized access to their energy levels, oxygen level, respiratory rate, stress levels, sleep patterns, and heart rate will promote behaviors that mitigate stress, resulting in improved well-being.

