Additionally, to preempt burnout among physicians, there is an urgent and unmet need for predicting imminent burnout. The National Academy of Medicine's consensus study on clinician burnout recommended that organizations regularly deploy surveys to measure and monitor physician well-being. Although surveys are an important tool, at best they prompt action in work units where quality of care has already suffered, and turnover or loss of productivity has already occurred due to high levels of burnout. Additionally, individuals are typically not made aware of their own level of distress because of completing an organizational survey. Physiologic parameters, collected from Smartwatches, may be able to predict burnout ahead of its observable manifestations. Such information could help individuals as well as organizations engage in proactive interventions to mitigate risk of future burnout, protecting patients and physicians. Burnout can be addressed and therefore, early identification could have a profound broad impact on physicians, patients, employers, and the global economy (improved productivity, work performance and reduced absenteeism).

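### Scoring Aim 2 on next-quarter status, with no split by status at the preceding survey, answers the formal aim but cannot by itself support the early-warning use described in the background

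*Protocol*

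**What the plan says.** **Formal aim.** Under Study Aims, Aim 2 asks whether continuous watch measures "contain a 'signal' that predicts physician well-being, and if so in which dimensions". The opening of section I and Hypothesis 3 speak in the same way of subsequent well-being. None of these mentions new onset.

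**Rationale.** Section II goes further. It states that "there is an urgent and unmet need for predicting imminent burnout", that watch data "may be able to predict burnout ahead of its observable manifestations", and that wearables may "forecast impending burnout or changes in other dimensions in well-being, potentially triggering individual intervention before suffering or negative impact to patient care occurs". Section IV.B justifies including residents and fellows partly by the prospect of technology that lets burnout be mitigated before it happens.

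**Scoring.** Section IV.F defines each dimension by a cut-off and then says "Data from Arm 1 will be used to train MTL models to predict risk of low well-being, burnout, low QOL, high stress, and high fatigue". The horizon is one quarter ahead, with testing and retraining as later surveys come in. Predictions are evaluated on Arm 2 data. AUC, sensitivity and specificity are given as example metrics, and the goal is accuracy above 70%. Nothing restricts or splits the evaluation by status at the preceding survey.

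**Population.** The eligibility criteria in section IV.B do not exclude physicians already above a cut-off, and section II opens with "Upwards of 40% of physicians have burnout".

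**The concern.** If burnout tends to last from one quarter to the next, many physicians who are positive at the next survey were already positive when the watch data were recorded. A watch feature that only detects current burnout would then earn a respectable next-quarter AUC without foreseeing a single new case.

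This is a different question from whether the watch carries any signal. The signal can be real and still not be early. What is at stake is interpretation: a good pooled result could be reported as showing that burnout can be forecast in physicians not yet affected, when the evaluation as written does not separate that from recognising burnout already present.

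**Working it through.** The protocol gives no derived figure to reproduce; the 70% accuracy goal is stated without inputs. The check is therefore a simple model of how a pure mirror of current status would score.

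**Inputs**
- Prevalence p = 0.40, from section II, assumed to apply to this sample and to be stable over time.
- Persistence s, the probability of burnout at the next survey given burnout now. It is not in the protocol; assumed 0.70 to 0.90.
- A, the AUC of the watch feature for current burnout. It is not in the protocol; assumed 0.80 to 0.90.
- No onset signal: given current status, the feature says nothing about next status. This is imposed, so its onset AUC of 0.50 is an input and not a result.
- Up to 184 participants and 15% drop-out, from section IV.B. Equal allocation is assumed, so 92 per arm and 92 × 0.85 = 78.2 remaining.

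**Pooled next-quarter AUC**

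With stable prevalence:
- a = P(burnout now | burnout next) = s
- b = P(burnout now | no burnout next) = p(1 − s)/(1 − p)
- Pooled AUC = a(1 − b)A + 0.5ab + 0.5(1 − a)(1 − b) + (1 − a)b(1 − A), which simplifies to 0.5 + (a − b)(A − 0.5)

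| s | b | a − b | A = 0.80 | A = 0.90 |
|---|---|---|---|---|
| 0.70 | 0.200 | 0.500 | 0.65 | 0.70 |
| 0.80 | 0.133 | 0.667 | 0.70 | 0.77 |
| 0.90 | 0.067 | 0.833 | 0.75 | 0.83 |

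Over the same ranges of s and A, p = 0.30 gives 0.67 to 0.84 and p = 0.50 gives 0.62 to 0.82.

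**Against the protocol's 70% accuracy goal (p = 0.40)**
- Carrying current status forward unchanged has accuracy 1 − 2p(1 − s): 0.68, 0.76, 0.84 and 0.92 for s = 0.60, 0.70, 0.80 and 0.90. It reaches 0.70 at s = 1 − 0.30/0.80 = 0.625, yet it identifies no new case.
- An imperfect binary mirror with sensitivity and specificity 0.85 for current status has accuracy 0.85c + 0.15(1 − c), where c is the carry-forward accuracy. This gives 0.63, 0.68, 0.74 and 0.79. It passes 70% at s = 0.80 and 0.90, and misses at 0.60 and 0.70.

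**Onsets available in Arm 2**
- At risk per quarter: 78.2 × 0.60 = 46.9.
- Onset probability, p(1 − s)/(1 − p): 0.067 to 0.20 for s = 0.90 to 0.70.
- Onsets per quarter: 3.1 to 9.4. Arm 2 wears the watch from month 6 to 9 and from month 9 to 12, so two quarters give about 6 to 19.

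**The case against.** The strongest reply is that the plan does what its aim asks. Aim 2, Hypothesis 3 and the summary in section IV.G concern a signal that predicts subsequent well-being, and next-quarter status addresses that directly. The early-warning language sits in the background and population sections, is partly hedged, and no aim or hypothesis refers to physicians not yet affected. This stands. A reader might infer that section IV.F fails Aim 2, or that a good pooled AUC would be worthless; the protocol supports neither. A reader might also take the model-building paragraph of section IV.C as a further early-warning promise, but it speaks only of predicting burnout.

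A second reply is that manifestations may mean lapses in performance, turnover or ill health, not crossing a survey cut-off. Section II says that burnout is under-recognised, so flagging a physician who is already above the cut-off but unaware of it would serve part of the purpose. This also stands in part, although the words impending and imminent, and the section IV.B rationale, point to onset as well.

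Third, section IV.F plans dynamic Bayesian networks and section IV.D lists survey scores among the inputs, so earlier status may enter the model. That changes what the model can use, not how its predictions are scored.

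Fourth, the lack of any restriction on who is scored is inferred from silence, the metrics are an open list, and a stratified table could sit in an analysis plan that is not shown. This limits the weight of the point. It is still worth raising, because the protocol itself fixes the target, horizon, validation cohort and accuracy goal.

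Finally, persistence and current-status AUC are assumptions, and only burnout is quantified out of five dimensions. With persistence of 0.60, even perfect carry-forward misses the 70% goal.

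**Conclusion.** The point holds as an inexpensive improvement, not as an error in the stated aim. Next-quarter status is a proper test of Aim 2. Without a split by status at the preceding survey, it cannot distinguish foreseeing burnout from detecting burnout already present, so it cannot alone carry the early-warning use described in sections II and IV.B.

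The size depends on figures that the protocol does not give. With prevalence 0.40, persistence 0.70 to 0.90, current-status AUC 0.80 to 0.90 and no onset signal, the pooled AUC is about 0.65 to 0.83. Lower persistence shrinks the problem. The calculation shows what a pure mirror could score; it is no evidence that the watch signal is one.

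**What to change.** Keep next-quarter status as the main Aim 2 result and add to section IV.F wording such as:

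> For each dimension, AUC, sensitivity and specificity will also be reported separately for person-quarters below and above the cut-off at the preceding survey, pooling the two Arm 2 watch quarters. Any statement about forecasting new burnout will rest on the below-cut-off result with its confidence interval. If that result is too imprecise, the conclusion will be limited to predicting next-quarter status.

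Because one physician can contribute two person-quarters, the interval should allow for repeated observations.

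No new data are needed, since the quarterly surveys already record status at the start of each quarter. The cost is one stratified table, wide intervals for onset (about 6 to 19 burnout events under the assumptions above) and possibly a narrower claim.

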**Hypothesis:**

1. Physicians with individualized access to their energy levels, oxygen level, respiratory rate, stress levels, sleep patterns, and heart rate will engage more frequently in behaviors that mitigate stress, resulting in improved well-being.
2. Fatigue, stress, and overall quality of life will improve while burnout will be less impacted by wearing a Smartwatch.
3. Physiologic parameters, collected from Smartwatches, will relate to physician's subsequent endorsement of symptoms of fatigue, stress level, and overall quality of life more closely than their measured symptoms of professional burnout.

In this study, physicians will be asked to wear a Smartwatch and answer a survey at baseline, 3-, 6-, 9-, and 12-months. We will determine if physicians who wear a Smartwatch and have access to its data experience greater improvements in their well-being relative to physicians not wearing a Smartwatch (control group). In addition, we will collect data from the Smartwatches to determine if we can utilize this data to predict subsequent level of well-being. We will build the

infrastructure and a HIPAA compliant de-identified dataset which includes (i) continuous physiology measures (from Smartwatches; raw data gathered for every 15-second epoch) and (ii) survey responses. We will use this dataset to develop predictive models for well-being derived from physiologic measures. Prediction models established using the cohort in Arm 1 will be validated in the cohort in Arm 2 after they cross-over (at the 6-month time-point) and begin using the Smartwatch.

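### Hypothesis 3 asks how closely watch data relate to levels of well-being, but the Aim 2 plan models only above/below-cut-off states; the numeric scores should be added as outcomes (minor).

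*Protocol*

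**What the plan says.** Section I of the Protocol describes the Aim 2 target in terms of degree. Hypothesis 3 expects watch parameters to relate to "subsequent endorsement of symptoms of fatigue, stress level, and overall quality of life more closely than their measured symptoms of professional burnout". The study description under the same heading says the data will be used to "determine if we can utilize this data to predict subsequent level of well-being". Aim 2 itself leaves the scale of the outcome open: it asks whether the measures "contain a 'signal' that predicts physician well-being, and if so in which dimensions".

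Section IV.F then fixes the outcomes as five states:
- low overall well-being: Well-Being Index score of 2 or more
- burnout: emotional exhaustion (EE) of 27 or more, or depersonalization (DP) of 10 or more
- low quality of life: at least half an SD below the mean
- high stress: score of 17 or more
- high fatigue: score of 11 or more

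Arm 1 data will be used to "train MTL models to predict risk of low well-being, burnout, low QOL, high stress, and high fatigue in the next quarter", and Arm 2 data to evaluate the predictions. The metrics named are AUC, sensitivity and specificity (as examples), with an aim of more than 70% accuracy. IV.F names no model for a numeric score and no comparison between dimensions. Section IV.D lists survey scores among the analytic inputs, so the numeric values will be in the dataset.

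**The concern.** Hypothesis 3 is a ranking claim: some dimensions are expected to track the watch data more closely than burnout does. A cut-off label is a coarse basis for that ranking. A one-point move across a cut counts as a full change, while a large move on one side counts as nothing. The labels also differ in kind. Burnout is positive if either of two subscales is high; the others are single cuts, and one of those is relative to the sample mean. A difference between dimensions in AUC or accuracy may therefore partly reflect how the labels were built.

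IV.F fixes the cut-offs, the model family, the validation arm and the accuracy target, so a later analysis plan that followed it would inherit the label outcomes. At stake is the chance of missing a moderate signal, or a real difference between dimensions, that the collected scores could show. The randomised comparison in Aim 1 is not affected.

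**Working it through.** **No figure to reproduce.** The protocol states no power, alpha or effect size for Aim 2. The enrolment of up to 184 (IV.B) cannot be rebuilt either, because its effect size and power are not given. It is compatible with a standardised difference of 0.45 at 80% power and two-sided 5%: 78 per arm, 78/0.85 = 91.8, so 92 per arm and 184 in total. That is back-solving, not a stated basis.

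**Inputs from the protocol.** Up to 184 participants and 15% dropout (IV.B); a half-SD quality-of-life cut (IV.F); "Upwards of 40% of physicians have burnout" (section II), the only prevalence given. Arm 2 receives watches after the 6-month survey and is surveyed again at 9 and 12 months (IV.C).

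**Assumed inputs.** 1:1 allocation, so 184/2 × 0.85 ≈ 78 in Arm 2; normal scores; prevalence of 20-50% for the information calculation and 20-40% for the stress label; all correlations below.

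**1. Information kept by a cut.** For a normal score cut at prevalence p, with z the matching normal quantile, the relative efficiency is φ(z)²/[p(1−p)].
- p = 0.50: 0.64
- p = 0.40: 0.62
- p = 0.30: 0.58
- p = 0.20: 0.49

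Two points lie close to the protocol's own figures. Burnout at 40% keeps about 62%, only approximately because the label is a composite. A half-SD cut on a normal score has p ≈ 0.31 and keeps about 58%.

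**2. Accuracy is not comparable across labels.** A model with no information that always predicts the commoner state is about 1 − 0.31 = 69% accurate for low quality of life and about 1 − 0.40 = 60% accurate for burnout. The 9-point gap runs in the direction Hypothesis 3 predicts, without any signal. AUC does not have this artefact.

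**3. Power to detect one signal, n = 78, r = 0.30.** On the score, Fisher z gives atanh(0.30) × √75 = 2.68, so power is Φ(2.68 − 1.96) ≈ 0.76. By AUC on a label it is about 0.49-0.57.

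**4. Power for a between-dimension contrast, n = 78, one prediction each.** Simulation of a watch score, stress, EE and DP as normal variables. EE/DP correlation is 0.6 and stress/burnout correlation 0.5. The burnout label is EE (32%) or DP (25%), about 41% combined. Power = Φ(mean difference/SD − 1.96).
- Labels, r 0.50 vs 0.20: AUC difference 0.134-0.152, SD 0.071-0.084. Taking the lower ends together, 0.134/0.071 = 1.89 gives 0.47; taking the upper ends, 0.152/0.084 = 1.81 gives 0.44.
- Scores, same setting: correlation difference 0.29-0.30, SD 0.104-0.106, power about 0.80-0.84 over repeated runs.
- r 0.40 vs 0.15: about 0.31-0.34 on labels and 0.64-0.66 on scores.

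**5. The same with two predictions each** (9 and 12 months, within-person correlation 0.5-0.7).
- r 0.50 vs 0.20: about 0.65-0.73 on labels and 0.91-0.96 on scores.
- r 0.40 vs 0.15: about 0.47-0.54 on labels and 0.78-0.86 on scores.

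Whether one or two predictions apply depends on how the next quarter is read. Watch data from months 6-9 predicting the 12-month survey gives one; each quarter's data predicting the survey that closes it gives two.

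**The case against.** The strongest defence is that risk status is a sensible target. Sections II and IV.C give early identification of at-risk physicians as the purpose, and an early-warning model naturally predicts a state. Aim 2 asks only whether there is a signal and in which dimensions, and a per-dimension AUC answers that in part. This stands, and it is a reason to keep the labels. Demoting them would be a preference, not a correction.

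Four stronger readings are tempting, and the protocol does not support them.
- **That Hypothesis 3 is tested on cut scores.** IV.F specifies no test of it; the metrics are examples, and a formal comparison may properly sit in an analysis plan that is not shown. What can be said is that label metrics are the only evidence IV.F provides for it.
- **That the sections flatly contradict each other.** Endorsing symptoms and a level of well-being are loose terms that do not by themselves fix a continuous endpoint. This is a mismatch of wording and target.
- **That the trial loses 36-51% of its information.** That is the complement of 64-49%, and it needs normal scores and 20-50% prevalence. Quality of life is a single 0-10 item, so normal theory is only illustrative there.
- **That power is about halved.** This is fair for the contrast with one prediction each. With two, the labels keep roughly 60-76% of the power on scores, and for a single association at r = 0.30 about 64-75%.

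The calculations also use a simple correlation model, whereas the plan uses multitask and dynamic Bayesian models.

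**Conclusion.** The concern holds as a mismatch between question and outcome. Hypothesis 3 and the study description ask about closeness of relation and level. IV.F models only five cut-off states of unlike construction and names only label metrics, although the scores are collected.

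With about 78 Arm 2 participants, the illustrative cost for a between-dimension contrast is power of about 0.3-0.5 on labels against 0.6-0.8 on scores with one prediction each. With two it is about 0.5-0.7 against 0.8-0.95. The direction of the loss is secure. Its size rests on assumed normality, prevalences, correlations and 1:1 allocation, and should be quoted only as a range.

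Severity is minor: section I describes the prediction work as exploratory, the advertising text in section H calls it a secondary purpose, and the randomised comparison is untouched.

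**What to change.** In IV.F, keep the five labels with their AUC, sensitivity, specificity and accuracy for at-risk prediction. Beside them:
- Add the numeric next-survey scores (Well-Being Index, EE, DP, quality-of-life item, Perceived Stress Scale, Epworth) as outcomes for the signal question and Hypothesis 3, through regression outputs in the multitask model.
- In Arm 2, report for each dimension the correlation between predicted and observed score.
- For Hypothesis 3, report the paired differences in that correlation (fatigue, stress and quality of life, each against EE and DP), with a bootstrap interval that resamples participants so that repeated surveys are handled correctly.

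The cost is a paragraph of text, some extra modelling and a second set of results to present. No new data, participants or visits are needed.
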